## 2 Methods and design

### 2.1 Study design and patient selection

The LONGAN trial is a prospective, multicenter, randomized, placebo-controlled, double-blind, parallel-group, superiority trial that enrolls patients from stroke and rehabilitation units in China. This study will be conducted at 15 sites across China. The primary objective of the trial is to test the hypothesis that LSZ capsule is superior to the placebo for increasing the proportion of favorable functional status, defined as a modified Rankin Scale (mRS) score ≤1 at 90 days. The secondary objective is the assessment of any other benefits or harms from the end of the treatment period up to 180 days after the stroke. Participants will be followed up at 30, 90 and 180 days after randomization (D30, D90 and D180, respectively) to collect efficacy and safety outcomes in person. Patient enrollment will begin in May 2022 and end in June 2023. Figure 1 presents a schematic diagram of the patient timeline. The trial was approved by the institutional review board of Dongzhimen Hospital, Beijing University of Chinese Medicine, Beijing, China and registered in public clinical trial database (No. 2021DZMEC-198-02; ClinicalTrials.gov Identifier NCT 05277311). We described this study protocol according to the SPIRIT 2013 Statement, and the complete checklist is available.

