### 2.4 Efficacy outcomes

The primary outcome will be the proportion of patients with a favorable outcome, which is defined as mRS ≤1 on D90 (Rankin, 1957). The mRS is an ordinal scale ranging from 0 to 6 (Lees et al., 2012), with 0–1 indicating no disability, 2 to 5 indicating disability (increasing from 2 to 5), and 6 indicating death. The secondary outcomes will be as follows: 1) distribution of mRS scores [will be measured on D30 and D90]; 2) proportion of patients with good functional status [defined as mRS score ≤2; will be measured on D30 and D90]; 3) neurological deficit improvement [defined as a change in the National Institute of Health Stroke Scale (NIHSS) score (Brott et al., 1989), ranging from 0 to 42, with higher scores indicating more severe strokes; will be measured at baseline, D30, and D90]; 4) proportion of poor health-related quality of life (poor-HRQOL) [available EuroQol-5D Questionnaire (EQ-5D) data will be used to calculate EQ-5D index scores (Dorman et al., 1997). Poor-HRQOL is defined as an EQ-5D index score ≤0.5 and will be measured on D30 and D90. The EQ-5D index score is measured on a scale between 0 (death) and 1 (full health). The patient’s mobility, self-care ability, daily activities, feelings of pain or discomfort, and feelings of anxiety or depression contribute to EQ-5D. Here, each aspect will be divided into three levels (Rabin and de Charro, 2001): no problems, moderate problems, or extreme problems. The EQ-5D index score (preference-based health status) will be determined using the population-based preference weight values for five dimensions of the scale (Dolan, 1997; Shaw et al., 2005; Liu et al., 2014). This study will use preference weights applicable to the Chinese population (Liu et al., 2014)]; 5) proportion of patients with functional independence [defined as Barthel Index (BI) ≥90 (Mahoney and Barthel, 1965); BI is a conventional scale used to assess the activities of the daily living of stroke patients involving 10 items with a maximum score of 100 points; will be measured on D30 and D90]; 6) changes in motor function [measured by the Fugl–Meyer Motor Scale (FMMS) score (Fugl-Meyer et al., 1975), ranging from 0 to 100, with lower scores indicating poorer motor status; the change from baseline of the FMMS will be measured on D90]; and 7) changes in cognitive function [measured by the Montreal Cognitive Assessment (MoCA) score (Nasreddine et al., 2005), ranging from 0 to 30, with less than 26 indicating cognitive impairment; the change in MoCA from baseline will be measured on D90].

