#### 2.12.5 Analysis of the secondary and exploratory outcomes

For dichotomous outcomes, including the proportion of patients of good functional status (mRS ≤2), the proportion of poor-HRQOL (EQ-5D index score ≤0.5), the proportion of patients with functional independence (BI ≥ 90), the distribution of mRS scores, recurrence rates of stroke, and the proportion of new combined vascular events, a comparison of how patients with these outcomes are distributed among the two groups will be assessed using a chi-square test or Fisher’s exact test and presented as OR estimates and 95% CIs using logistic regression. Moreover, the distribution of functional outcomes on the mRS in both groups will be expressed in histograms. For other secondary outcomes of continuous variable, the changes from baseline to the endpoint of treatment for the above outcomes, including neurological deficit, motor function and cognitive function will be analyzed using the Student’s t test or Wilcoxon rank-sum test where appropriate. For survival data, the Kaplan-Meier method will be used to estimate the survival rate of each group; a survival curve will be drawn, and the log-rank test will be used to evaluate the curative effect. Cox proportional hazards models will be used to calculate hazard ratios (HR) and 95% CIs between the two treatment regimens. The central effect will be set as a random effect in all models. All statistics will be evaluated using two-sided tests, and *p* < 0.05 will be considered statistically significant.

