#### 2.12.7 Subgroup analyses

A subgroup analysis of the primary objective will be conducted based on the following patient baseline characteristics: age (<65 and ≥65 years), sex (female and male), medical history, TOAST classification, and NIHSS score.

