To our knowledge, the LONGAN trial is the largest prospective, multicenter, randomized, placebo-controlled, double-blind, parallel-group, superiority trial to assess the efficacy and safety of LSZ capsule in patients with AIS. The study has potential to answer the vexing question of whether LSZ can improve functional recovery in AIS patients. We anticipate LONGAN to be a landmark herbal study and an expected conclusive “end of discussion” report of LSZ. Among that, LONGAN will be conducted on China Stroke Registry for Patients with Traditional Chinese Medicine (CASES-TCM) platform which was the largest nationwide registry (Feng et al., 2021). Participating sites which were required to admit over 100 cases of patients with stroke per year formed a network across the country and offer a wealth of cases. All these strengths and resources will ensure that the LONGAN trial can be completed in a relatively short period of time. The ongoing COVID-19 pandemic has a potentially negative impact on the management of clinical trials. A more flexible approach removing unnecessary barriers may improve enrollment and access to the LONGAN, such as remote monitoring and tele-health visits. Also, this proposed study has two limitations. First, it will not be possible to follow up imaging changes in each patient due to funding constraints. Second, the treatment period will be 90 days and the follow-up period will be 180 days which is relatively short. Due to the limited time frame, the potential roles of LSZ in reducing overall mortality and future major vascular events will be uncertain, and further data on long-term clinical efficacy and safety will be needed. In conclusion, the LONGAN trial will further provide critical and high-quality clinical evidence for the target population of LSZ capsule for patients with mild-to-moderate AIS, regardless of whether the patients have experienced revascularization treatment or not.

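### Section 2.12.5 calls every test significant at two-sided p < 0.05, which covers 12 (or 11) secondary tests with no gate on the primary, no order and no descriptive status

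*Protocol article*

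**What the plan says.** Section 2.4 names one primary outcome (mRS ≤1 at D90) and seven secondary outcomes. The first five are read at two visits:

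- mRS distribution: "distribution of mRS scores [will be measured on D30 and D90"
- good functional status: "defined as mRS score ≤2; will be measured on D30 and D90"
- NIHSS change: "will be measured at baseline, D30, and D90"
- poor quality of life (EQ-5D index ≤0.5): D30 and D90
- Barthel Index ≥90: D30 and D90

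Change in FMMS and change in MoCA are secondary outcomes at D90 only.

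Section 2.12.5 gives the methods for secondary and exploratory outcomes together and closes with the decision rule: "All statistics will be evaluated using two-sided tests, and *p* < 0.05 will be considered statistically significant". The article gives no testing order, no split of alpha, no requirement that the primary be met first, and no statement that secondary p-values are descriptive. The exploratory label in Section 2.5 belongs to a separate list (imaging, D180 and vascular outcomes), not to the seven secondary outcomes.

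**The concern.** The sentence in Section 2.12.5 is more than silence on multiplicity. It says what significance means, and says so for all statistics. Followed as written, it lets any one of the secondary tests be reported as a statistically significant benefit even when the primary comparison fails.

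That sits badly with the article's stated purpose. The abstract and Section 3 say that the analyses are pre-specified to limit selective, data-driven reporting, and Section 3 expects a conclusive result: "We anticipate LONGAN to be a landmark herbal study and an expected conclusive “end of discussion” report of LSZ". With a dozen unranked tests at full alpha, the choice of which secondary result to feature is left until the data are known. The D30 readings add five tests of outcomes that are tested again at D90.

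**Working it through.** **Plan's own figure.** The article gives no family-wise error rate for the secondary outcomes, so there is none to reproduce. The two-sided 5% in Section 2.11 belongs to the sample size for the primary outcome.

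**Number of tests (Section 2.4).** Five outcomes × 2 visits + two outcomes × 1 visit = 12. Section 2.12.5 describes the continuous outcomes, including neurological deficit, as changes from baseline to the end of treatment. Read literally, NIHSS is then tested once, at D90, and the count is 11.

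**Independent tests, no true effect.**

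- Either direction, k = 12: 1 − 0.95^12 = 0.460. For k = 11: 1 − 0.95^11 = 0.431.
- In favour of LSZ only (2.5% per test), k = 12: 1 − 0.975^12 = 0.262. For k = 11: 1 − 0.975^11 = 0.243.

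**Correlated tests.** The outcomes are clearly related: two come from the same scale, and five are repeated readings. The article gives no correlation, so a common correlation ρ between the test statistics is assumed and varied. Each test is treated as a standard normal statistic with critical value c = 1.96. Then

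P(at least one, either direction) = 1 − ∫ φ(u) [Φ((c − √ρ·u)/√(1−ρ)) − Φ((−c − √ρ·u)/√(1−ρ))]^k du.

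For results in favour of LSZ only, the second Φ term is dropped.

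| ρ (assumed) | 12 tests, either direction | 12 tests, favouring LSZ | 11 tests, either direction |
|---|---|---|---|
| 0 | 0.460 | 0.262 | 0.431 |
| 0.3 | 0.397 | 0.202 | 0.375 |
| 0.5 | 0.319 | 0.160 | 0.304 |
| 0.7 | 0.232 | 0.116 | 0.223 |
| 0.9 | 0.135 | 0.067 | 0.131 |

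Simulation with 500,000 draws agrees with the either-direction columns to within about 0.002.

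**A less uniform structure.** With correlation 0.3 to 0.7 between outcomes and 0.6 to 0.8 between visits, multiplied for pairs that differ in both, 12 tests give 0.24 to 0.39 in either direction.

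**D90 alone.** Dropping the D30 tests leaves seven. In either direction these give 1 − 0.95^7 = 0.302 if independent and 0.230 at ρ = 0.5. Removing the D30 tests therefore lowers the figure but does not solve the problem.

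**The case against.** **The full SAP may settle it.** A testing order for secondary outcomes is often left to the SAP, which is not shown, and the article says that it summarises the plan for the primary analysis. This has weight, and the absence of a hierarchy alone would not be a finding. But the article states a rule covering all statistics. A hierarchy elsewhere would have to restrict that sentence, and readers of the article would still hold the unrestricted version.

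**The trial's main conclusion is safe.** This stands. There is one named primary outcome, and the secondary tests do not touch its type I error. The expectation of a conclusive report follows a sentence about functional recovery and makes no claim about the Barthel Index, FMMS or MoCA. Reading secondaries as supportive, without a gate, is also a legitimate choice, provided that the plan says so.

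**Stronger readings that the documents do not support.**

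- A reader might take one in three as the false-positive chance. That needs an assumed correlation near 0.5 and counts results favouring placebo. For a false claim of benefit, the figure at that correlation is 16%.
- A reader might infer that any given significant secondary result is probably false. The calculation does not show this. Each test keeps its 5% error rate under the null; what rises is the chance of at least one such result in the set.
- A reader might add the D180 outcomes to the count. Section 2.5 already calls them exploratory, so they lack the main defect, although Section 2.12.5 applies the same threshold to them.
- A reader might extend the point to subgroups. Section 2.12.7 says only that "A subgroup analysis of the primary objective will be conducted based on the following patient baseline characteristics" and lists the factors. It states no within-level tests and no subgroup claim, so an error rate there would rest on invented inputs.

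**Conclusion.** The point holds, limited to claims on secondary outcomes. The error rate exceeds 5% at every correlation examined, in either direction and in favour of LSZ alone, but its size depends on that assumed correlation and on treating the tests as equicorrelated normal statistics under a global null. Whether NIHSS is tested once or twice changes little. The exposure is greatest when the mRS ≤1 primary fails and a secondary result is put forward in its place. This should be corrected; it does not threaten the validity of the primary analysis.

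**What to change.** In Section 2.12.5, limit the p < 0.05 significance rule to the primary outcome, then choose one of two routes for the seven D90 secondary outcomes:

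1. Test them for significance only if the primary is significant, either in a fixed sequence written down before unblinding or by Holm's method, at the primary's final two-sided alpha. In the fixed sequence, formal testing stops at the first non-significant result.
2. Report them as supportive, with estimates and 95% CIs and no significance label. This changes how the results may be described, not their error rate.

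Under either route, report the D30 secondaries, and the D180 outcomes already called exploratory, with estimates and 95% CIs and without describing them as statistically significant. State also whether NIHSS change is analysed at D30 as well as D90, so that the set of tests is fixed.

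The cost is a few sentences before unblinding, with no extra patients, visits or data. The downside is that D30 results, and secondaries low in a sequence, can no longer be called significant on a nominal p < 0.05.

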#### 2.12.6 Analysis of safety outcomes

Based on the SS data set, the method of statistical description will be used, and the differences in the incidence of primary and secondary safety endpoints will be compared between the two groups. For most safety endpoints, HR values between the two treatment regimens will be calculated using Cox proportional hazards models; Poisson regression or negative binomial regression will be used for rare events. AEs and SAEs will be listed separately, and a summary analysis will be performed. Within each treatment group, the number and proportion of AE cases will be aggregated separately by tissue system classification and by items of interest. In addition, all deaths and SAEs will be described in detail using case narratives.

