### 2.6 Safety outcomes

The main safety outcome is the proportion of SAEs. Other safety outcomes include any adverse events (AEs) and clinically meaningful changes in vital signs or laboratory parameters during the study period.

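### Poisson or negative binomial regression is the stated model for rare safety events, where its usual large-sample p-values and confidence intervals are unreliable (minor)

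*Protocol article*

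**What the plan says.** Section 2.12.6 of the protocol article divides the safety models by how common the event is. The general rule is that "For most safety endpoints, HR values between the two treatment regimens will be calculated using Cox proportional hazards models". The exception follows directly: "Poisson regression or negative binomial regression will be used for rare events". The section does not define a rare event, does not say how to choose between the two count models, and does not name the type of inference (Wald, likelihood-ratio, score or exact).

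Three other statements bear on the point:

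- Section 2.6: "The main safety outcome is the proportion of SAEs". The headline safety measure is thus a share of patients.
- Section 2.12.6 also plans that "the differences in the incidence of primary and secondary safety endpoints will be compared between the two groups", without naming a test.
- Section 2.12.5 says that dichotomous secondary and exploratory outcomes "will be assessed using a chi-square test or Fisher’s exact test", and adds: "The central effect will be set as a random effect in all models". Fisher's test is not repeated for safety.

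**The concern.** Most rare safety outcomes are yes/no per patient, with a handful of events in the whole trial. The article names an exact test for its binary secondary and exploratory outcomes, several of which will have ample counts. For the outcomes with the smallest counts it names only regression models whose usual p-values and intervals rely on large samples.

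What is at stake is the inferential statement attached to a small one-sided cluster of events. Depending on an option that the article leaves open, the same data could be reported as no evidence at all or as a significant difference that an exact test does not support.

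**Working it through.** **Inputs.** Recruitment target 1,376 and 1:1 allocation (Section 2.11), so 1,376 / 2 = 688 per arm. The target follows from the article's own figures: 1,238 / (1 − 0.10) = 1,375.6, rounded up to 1,376. Tests are two-sided at 0.05 (Section 2.12.5). The article gives no expected rate for any safety event, so the event counts and risks below are assumptions. All calculations omit covariates and the centre effect and take equal follow-up in the arms.

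**Step 1: Wald inference with an empty arm.** For *a* and *b* events in equal arms, the Poisson log rate ratio is ln(*a*/*b*), with standard error √(1/*a* + 1/*b*). At *b* = 0 both are infinite. Software stops at an arbitrary value: for 6 against 0, an estimate of about 31 with a standard error above 1,000,000, hence p = 1.000. Negative binomial regression with dispersion fixed at 1 (an assumption) does the same.

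**Step 2: other tests on the same data.** For *k* against 0 in equal arms:

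- Poisson likelihood-ratio statistic = 2*k* ln 2, on 1 degree of freedom. For *k* = 3 it is 4.16; for *k* = 6 it is 8.32.
- Exact conditional Poisson p = 2 × 0.5^*k*. For *k* = 6 it is 0.031.
- Fisher p = 2 × C(688, *k*) / C(1376, *k*).

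| Events | Wald p | Likelihood-ratio p | Fisher p | Exact conditional Poisson p |
|---|---|---|---|---|
| 3 vs 0 | 1.000 | 0.041 | 0.249 | 0.250 |
| 4 vs 0 | near 1 | 0.019 | 0.124 | 0.125 |
| 5 vs 0 | 1.000 | 0.008 | 0.062 | 0.063 |
| 6 vs 0 | 1.000 | 0.0039 | 0.031 | 0.031 |
| 8 vs 0 | 1.000 | 0.0009 | 0.0077 | 0.0078 |
| 10 vs 0 | 1.000 | 0.0002 | 0.0019 | 0.0020 |

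An exact interval stays informative: at 10 vs 0 the lower 95% limit of the rate ratio is 2.24. With 619 per arm the results are practically the same.

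**Step 3: true size of the likelihood-ratio test.** With the same risk *p* in both arms, sum Bin(*a*; 688, *p*) × Bin(*b*; 688, *p*) over all pairs (*a*, *b*) where the test gives a p-value below 0.05. The result is 8.3%, 9.7% and 8.2% at *p* = 0.2%, 0.3% and 0.5%, against a nominal 5%. The same sum for Fisher's test gives 0.15%, 0.55% and 1.5%, so the exact test errs on the conservative side.

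**Step 4: how often an arm is empty.** With *q* = (1 − *p*)^688, the chance that exactly one arm has no event is 2*q*(1 − *q*). This is 38% at *p* = 0.2%, 6% at 0.5% and 0.2% at 1%.

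**Step 5: is this peculiar to count models?** No. For 6 against 0, logistic regression gives Wald p 1.000 and likelihood-ratio p 0.0039, and a Cox model gives 1.000 and 0.004.

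**The case against.** A reader might infer that these models collapse with rare events and that a clear safety signal would be reported as p near 1. The documents do not support that reading, for four reasons.

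- **Wald is not prescribed.** Section 2.12.6 names a model family and no test statistic. The divergence affects the maximum-likelihood estimate and Wald inference; likelihood-ratio and exact conditional inference from a Poisson model can still be computed.
- **The imbalance would stay visible.** The same section says that "the number and proportion of AE cases will be aggregated separately by tissue system classification and by items of interest" and that "all deaths and SAEs will be described in detail using case narratives". The planned comparison of incidences names no test and could be Fisher's. An independent monitoring board also reviews safety data (Section 2.9).
- **Empty arms are a general problem.** Step 5 shows that Cox and logistic models share it, so it is no special defect of count regression.
- **Count models have a proper use.** Adverse events can recur, and follow-up will vary with 10% loss expected. A Poisson rate with person-time then fits well beside the hazard ratios used for other endpoints, whereas Fisher's test ignores exposure time.

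All four stand. It is also true that the random centre statement sits in Section 2.12.5, so carrying it into the safety section is an inference, and non-convergence with a centre effect over 15 sites was not calculated.

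Two further replies do not remove the point. Turning to the likelihood-ratio test replaces a p-value that hides a difference with one that overstates it (Step 3). And although a condensed article may leave the test statistic and zero-event handling to the full plan, this article does fix the model for rare events, and that choice can be judged as stated.

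**Conclusion.** The point holds in a limited form, as a minor one. For rare events, both usual ways of running the stated model mislead. Wald inference gives p near 1 whenever an arm is empty, even at 10 against 0. Likelihood-ratio inference is anti-conservative, with true size of about 8 to 10% at assumed risks of 0.2 to 0.5%.

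The damage is confined to the p-value and confidence interval reported for very rare event types. It does not reach disclosure of the events. Nor does it reach the main outcome of serious adverse events unless those prove extremely rare: at an assumed shared risk of 1%, exactly one arm would be empty with a chance of only 0.2%.

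The figures rest on 688 patients per arm with equal follow-up, no covariates and no centre effect. The event risks are illustrative and do not come from the documents.

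**What to change.** In Section 2.12.6, replace the sentence on rare events with a rule set in advance:

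- When either arm has few observed events (for example fewer than 5, including none), compare the arms with Fisher's exact test, or with the exact conditional Poisson test if person-time is used. Report an exact 95% confidence interval and fit no random centre effect.
- Keep Poisson or negative binomial regression for recurrent event counts with enough events to fit.

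The trigger should be the observed count in either arm and not the expected count. With 10 events against 0 the expected count under no difference is 10 / 2 = 5 per arm, so a limit of fewer than 5 expected events would miss that case.

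The cost is one sentence, and Fisher's test is already named in Section 2.12.5. The downsides are that rare events get no centre adjustment and that the exact test is somewhat conservative. No change to data collection or sample size is needed.
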